#### Participant timeline {13}

The overall participant timeline is illustrated in Fig. 1.

**Fig. 1 Fig1:**
[figure not shown]
SPIRIT schedule of enrollment, intervention, and assessments

Week 0 (T1): Eligible participants who consent to randomization and to participate in the program will receive notice of enrollment. Participants will participate in a clinical orientation meeting with a member of the clinical research team (i.e., a parent or clinical coach) and complete the pre-test assessments, including primary, secondary, and exploratory outcome measures.

Week 1: Participants randomized to the experimental condition will receive an email regarding login and account information. Program information will be sent electronically to participants from the study team, and participants will watch introductory videos to become familiar with the app. Participants will begin engaging in the forum.

Weeks 2–11: Participants will watch weekly videos and will complete mood tracking questions on depression and anxiety symptoms, parenting stress, recent stressful experiences, and positive mood for self-monitoring purposes. Participants will also participate in weekly Zoom telehealth group sessions and continue engaging in the forum.

Weeks 12–16 (post, T2): Participants will complete a full post-test assessment of primary, secondary, and exploratory outcome measures.

Month 6 (follow-up, T3): Participants will complete a follow-up assessment of primary and secondary outcome measures.

#### Sample size {14}

Based on the findings from a meta-analysis, digital interventions for depression that include a human therapeutic guidance component (as is the case with the BEAM program group therapy sessions) have a moderate effect on depression (*g* = .63) [78]. Thus, an a priori, one-tailed, two-group power analysis was conducted using a moderate effect size (*d* = .5) using the G* Power 3 software [79]. The power analysis indicated that we would need 51 participants per group to reach 80% power (*α* = .05) to detect a clinically significant change in depression. To account for anticipated attrition of approximately 25%, a total sample of 140 with 70 in each group (intervention and control) will be the target for recruitment.

#### Recruitment {15}

Participants in Alberta and Manitoba, Canada, will be recruited online via multiple sources such as advertisements on social media platforms including the Hearts and Minds Research Lab Facebook, Twitter, and Instagram accounts. Recruitment materials will also be emailed to relevant community agencies and daycares. Individuals will respond to program advertisements by clicking a link to the online eligibility screener. Individuals who meet all the eligibility criteria and consent to randomization will be invited to participate in the study. The recruitment duration period will last 3 months, and recruitment will be monitored by the research staff. Participants will be eligible to receive up to $150 Canadian (CAD) compensation for their enrollment and participation for the entire study duration. There are no incentives provided to trial investigators for participant enrollment.

### Assignment of interventions: allocation

#### Sequence generation {16a}

Allocation will be conducted using a randomized intervention model. Participants will be randomly allocated in a 1:1 ratio to the BEAM program or TAU. Randomization will be stratified based on which telehealth group timeslot participants identified being available for. Central randomization, by computer-generated sequencing using an online tool (https://www.randomlists.com/team-generator), will be conducted by a research assistant that is not affiliated with the BEAM clinical research team.

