### Outcomes {12}

#### Primary outcomes

The primary outcome is mean change in depression symptoms from pre- to post-intervention and from pre-intervention to follow-up, assessed using the Patient Health Questionnaire-9 (PHQ-9) [57], a self-report questionnaire that measures depression severity. Participant depression symptoms will be measured during eligibility screening pre-intervention (T1), immediately after intervention (T2), and at a 6-month follow-up (T3). The PHQ-9 includes nine items, asking participants to report over the past week how often they have been bothered by certain problems. Participants respond to each item using a 4-point Likert scale ranging from 0 (*not at all*) to 3 (*nearly every day*). Possible scores range from 0 to 27, with higher scores indicating more severe depression symptoms. Participant scores are summed, and a cutoff score of ≥ 10 will be used to identify participants who present with clinically concerning symptoms of depression [57]. The PHQ-9 cutoff score of 10 has been shown to demonstrate high sensitivity and specificity in detecting depression in a perinatal population [58].

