## Statistical methods

### Statistical methods for primary and secondary outcomes {20a}

Between-group differences in primary and secondary outcome variables, as well as quantitative exploratory outcome variables (observational and Fitbit data), will be analyzed using linear mixed models. Models will test both a linear and quadratic time coefficient, where quadratic time coefficients will be removed from final models if not significant. An *α* of 0.05 will be used to determine statistical significance. Effect sizes of 0.20, 0.50, and 0.80 will be interpreted as indicating small, medium, and large effects, respectively [80]. Standardized effect sizes for linear mixed models will be derived based on existing recommendations for linear mixed models [80, 81]. The research team will also investigate if there is baseline moderation by symptom severity to examine whether the BEAM intervention is more effective than the control group for participants who have higher symptom levels at pre-intervention (e.g., depression, anxiety, insomnia).

Exploratory qualitative data will be analyzed thematically [82]. First, two analysts will concurrently, but independently read the transcripts for surface descriptive content, and organize like-with-like ideas. Second, transcripts will be re-read for latent meaning to better understand participants’ meaning, including looking for contradictory or confirmatory statements. Each analyst will independently generate and systematically apply themes across all transcripts. Semantic validity checks will ensure different words and phrases within a category have similar meanings [82]. To further enhance rigor, constructs will be deemed saturated (akin to statistical significance in quantitative work) when no new or additional constructs are identified, consensus is reached on all overarching themes, and no alternative explanations were found with subsequent interviews [82].

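### The mixed model takes T1 as a response but specifies neither a common T1 mean across arms nor the stratifying timeslot, so precision available from randomisation may be forgone

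*Protocol article*

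**What the plan says.** Under Sequence generation {16a} the protocol states: "Randomization will be stratified based on which telehealth group timeslot participants identified being available for". Trial design {8} also says that randomisation is stratified on telehealth availability.

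Under Primary outcomes: "The primary outcome is mean change in depression symptoms from pre- to post-intervention and from pre-intervention to follow-up".

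Under Statistical methods {20a}, the comparison of the two arms is described thus: "in primary and secondary outcome variables, as well as quantitative exploratory outcome variables (observational and Fitbit data), will be analyzed using linear mixed models". The models test linear and quadratic time, and the quadratic term is removed if it is not significant. That section names no covariates, no stratum term and no treatment of the T1 means. It excludes none of these either.

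There are three assessments of the primary outcome: T1, T2 and T3. Section {20c} adds intention-to-treat analysis with maximum likelihood. Sample size {14} rests on "an a priori, one-tailed, two-group power analysis was conducted using a moderate effect size" and takes no credit for baseline or repeated measurements.

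**The concern.** Three assessments can support a quadratic in time only if T1 is one of the responses. The role of T1 is therefore settled by the text, while the handling of its mean in each arm is not.

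If each arm has its own T1 mean, the treatment effect at T2 is a difference in change from T1, and any chance imbalance at T1 passes into it. Randomisation makes the expected T1 means equal. A model that uses this is at least as precise, and clearly more so when T1 and T2 are only moderately correlated.

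The stratification factor is a smaller matter of the same kind: a factor that restricted the randomisation would normally appear in the model.

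Precision is at stake, not bias. Discretion is a second issue, because section {17a} says the data analysts are members of the research team and are not blinded. The choice between free and common T1 means can move a result across 0.05, so it should be fixed in writing before analysis.

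**Working it through.** **The plan's own figure.** Inputs from Sample size {14}: d = 0.5, one-tailed α = 0.05, 80% power. A one-sided two-sample t test reaches 80.6% at 51 per group and 79.9% at 50, so "51 participants per group to reach 80% power" reproduces. With 25% attrition, 51 / 0.75 = 68 per group, or 136 in total. The target of 140 covers this.

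**Inputs for the check.** There are 70 randomised per arm, of whom 70 × 0.75 = 52.5 have T2 and T3 and 17.5 have T1 only. The effect at T2 is 0.5 SD, with SD 1 at each visit. The T1–T2 correlation ρ is an assumption, taken as 0.3 to 0.6. The model keeps group-by-linear and group-by-quadratic time, which fits the three means in each arm exactly.

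**Variance of the treatment effect at T2 (maximum likelihood).**

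- Common T1 mean: V_c = 2(1 − ρ²) / 52.5
- Free T1 means: V_f = V_c + 2(1 − ρ)² / 70

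The second term of V_f is the contribution of the chance T1 difference. It is never negative, so the free model is never the more precise. With complete data the ratio V_c / V_f reduces to (1 + ρ) / 2.

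Example at ρ = 0.5: V_c = 2 × 0.75 / 52.5 = 0.02857, SE 0.1690. V_f = 0.02857 + 2 × 0.25 / 70 = 0.03571, SE 0.1890. Two-sided power is Φ(0.5 / SE − 1.96). The one-sided version replaces 1.96 by 1.645.

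| ρ (assumed) | V_f | V_c | Two-sided power, free | Two-sided power, common | One-sided power, free | One-sided power, common |
|---|---|---|---|---|---|---|
| 0.3 | 0.0487 | 0.0347 | 62.0% | 76.6% | 73.3% | 85.1% |
| 0.4 | 0.0423 | 0.0320 | 68.1% | 79.8% | 78.4% | 87.5% |
| 0.5 | 0.0357 | 0.0286 | 75.4% | 84.1% | 84.2% | 90.5% |
| 0.6 | 0.0290 | 0.0244 | 83.6% | 89.3% | 90.2% | 94.0% |

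A numerical generalised least squares fit over the three visits gives the same variances.

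**Timeslot.** Suppose timeslot explains a share R of the variance at every visit (assumed; the protocol gives neither R nor the number of slots). The within-slot correlation is then (ρ − R) / (1 − R).

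- Free T1 means, complete data: the variance of change within slots is 2(1 − R)[1 − (ρ − R)/(1 − R)] = 2(1 − ρ). This equals the value without timeslot, because a stable slot effect cancels from the change. The gain is zero.
- Common T1 mean: the residual variance becomes (1 − R)[1 − ((ρ − R)/(1 − R))²] in place of 1 − ρ². At ρ = 0.4 and R = 0.10 this is 0.80 against 0.84, and two-sided power rises from 79.8% to 81.7%. Over ρ = 0.4 to 0.6 the gain is 0.4–0.9 points at R = 0.05 and 0.8–1.9 points at R = 0.10. At ρ = 0.3 and R = 0.10 it is 2.5 points.

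These figures ignore the degrees of freedom spent on slot terms.

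**The case against.** The strongest reply is that section {20a} is silent, not contrary. A condensed article gives no model equation, and covariates or a baseline constraint are often left to an analysis plan, which is not shown here. This stands in part: the protocol cannot be said to have rejected either term, and the point is that it specifies neither. The reply does not dispose of the matter, because the outcome definition and the time terms already make T1 a response. On that footing, the usual fit with a group effect at T1 gives the less precise contrast.

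Several stronger readings are tempting, and the documents do not support them:

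- **That the change would recover most of the lost power.** On its own one-tailed terms the sample size reproduces, so no power is lost. A shortfall appears only if the analysis, where an α "of 0.05 will be used to determine statistical significance" with no side stated, is two-sided. An unadjusted test at 51 per group then has 70.6%. How much the baseline recovers depends on a correlation that is not given.
- **That it costs nothing.** Slot terms use degrees of freedom, and the number of slots is not stated.
- **That PHQ-9 is truncated at 10, making a low correlation likely.** Entry is on depression and/or anxiety, so a mother who qualifies on GAD-7 can enter with PHQ-9 below 10.
- **That a model with only T2 and T3 as responses and T1 as covariate is equivalent.** It drops participants with T1 alone, whereas section {20c} includes every randomised participant's data.

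The power figures also assume that the quadratic term is kept. If it is dropped, the contrast is a slope through all three visits and its power depends on the assumed course to T3, so the figures do not carry over.

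**Conclusion.** The point holds as an efficiency and pre-specification matter of moderate weight. It is not an error that invalidates the analysis: free T1 means and an omitted stratum do not bias the comparison.

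For an assumed correlation of 0.3 to 0.6, a common T1 mean adds about 15 to 6 points of two-sided power, with the larger gain at the lower correlation. The one-sided gain is about 12 to 4 points, so the direction does not depend on how the sidedness question is settled. Timeslot is secondary. It adds nothing to a free-mean change contrast and, with a common mean and a correlation of 0.4 to 0.6, at most about 2 points. Its case rests mainly on its having been a stratification factor.

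The sizes rest on equal variances, d = 0.5 at T2, 25% of participants with T1 only, and the assumed correlation. That the constraint never loses precision does not depend on the value of the correlation.

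**What to change.** Add to Statistical methods {20a}, or to the analysis plan if one exists, before analysis: the linear mixed model constrains the two arms to a common mean at T1 (a constrained longitudinal model with no group effect at T1), keeps every randomised participant with any assessment, including those with T1 only, and includes telehealth timeslot as a fixed effect because randomisation was stratified by it. Apply the same form to every outcome measured at T1.

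Any statement of the expected gain should be conditional on an assumed T1–T2 correlation and shown over a range.

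The cost is a sentence of wording and a few degrees of freedom for the slot terms. No new data are needed: T1 scores and timeslot are already recorded.

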#### Concealment mechanism {16b}

Central randomization using computer-generated sequencing will be conducted by a research assistant who is not involved in clinical care (i.e., group therapy sessions, forum engagement) or pre- and post-test assessments to ensure allocation concealment.

#### Implementation {16c}

A research staff member who is not associated with the study will conduct the randomization and sequence generation. After the completion of the pre-test assessment, a research assistant will enroll participants in the trial, check the computer-generated assignment and inform participants of their enrollment and condition in the trial.

### Assignment of interventions: blinding

#### Who will be blinded {17a}

Participants, clinical coaches, and parent coaches will not be blinded to condition. Data analysts will not be blinded to conditions either as the analysis will be conducted by the research team. The trial did not have the funding for separate statisticians. The research assistants responsible for coding observational measures in assessments will be blinded to participants’ group assignments.

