### Methods for additional analyses (e.g., subgroup analyses) {20b}

Subgroup analyses will be conducted to explore the differences in outcomes for those who do and do not attend telehealth sessions regularly. Additional subgroup analyses may be explored based on emergent research questions of interest.

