### Plans to give access to the full protocol, participant-level data, and statistical code {31c}

The full trial protocol will be made publicly available through BMC Trials. [name] and [name] will remain the custodians of the data, as the primary investigators. Data will be analyzed independently and will not be released to any third party (including the funder) before the trial is completed. In accordance with the International Committee of Medical Journal Editor’s guidelines, the authors will share de-identified patient data that underlies results presented in reports no later than 6 months after publication. The primary investigators will ensure data is available upon request.

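### Lack of money for a separate statistician does not explain why the in-house analysts must see which arm is BEAM; coding the arms A/B for the main models would remove an avoidable risk of bias at little cost

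*Protocol article*

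**What the plan says.** Section {17a} of the protocol article sets out who is and is not masked:

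- Trial participants and programme staff: "Participants, clinical coaches, and parent coaches will not be blinded to condition".
- Analysts: "Data analysts will not be blinded to conditions either as the analysis will be conducted by the research team". The reason follows: "The trial did not have the funding for separate statisticians".
- The one masked group: "The research assistants responsible for coding observational measures in assessments will be blinded to participants’ group assignments". The Trial design section classes the outcomes they code as exploratory.

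Under Primary outcomes, the PHQ-9 is described as "a self-report questionnaire that measures depression severity", so the primary outcome is rated by the unblinded participant.

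Three other sections bear on whether masking is practicable. Under Sequence generation {16a}, randomization "will be conducted by a research assistant that is not affiliated with the BEAM clinical research team". The Confidentiality section {27} says that downloaded questionnaire data carry only de-identified ID numbers. Under Statistical methods {20a}, linear mixed models are used for the primary and secondary outcomes, and a quadratic time term is dropped when it is not significant.

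**The concern.** The reason given and the decision taken are about different things. Funding determines who does the analysis. Whether that person sees the arm labels is a separate question, and the section offers no reason for showing them.

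This matters more here than in many trials. Participants and coaches know the allocation and the primary outcome is self-reported, so the analysis is one of the few stages where masking is still possible. The research team developed the programme and will also analyse it. An analyst who knows the arms can lean towards the favoured answer, knowingly or not, in decisions on data cleaning, scoring and model checking.

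This is not a detail left to a statistical analysis plan. The article positively fixes unblinded analysis, and a later plan could not mask the analysts without departing from it.

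**Working it through.** The plan states no figure for analyst bias, so there is none to reproduce. Masking the arm code changes neither sample size, alpha nor power. The check is a comparison of sections plus one count.

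**1. Does the stated reason require arm labels to be visible?** No. Section {17a} itself keeps research assistants masked while they code the observational measures, with no claim that this needs extra funding. By its own account the trial can mask its own staff. It does so for exploratory outcomes and not for the analysis of the primary one.

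**2. Is masking practicable?**
- Sections {16a} and {16b} place the randomization with a research assistant outside the clinical team and outside the assessments. Such a person could supply a recoded file.
- Under {27}, questionnaire data are already held by ID number, so an A/B variable can be merged by ID.
- The telehealth timeslot used for stratification is recorded before randomization for both arms, so it can stay in the masked file.

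**3. What stands in the way?**
- Under {16c}, a research assistant checks each assignment and tells the participant.
- Under {21a}, the primary investigators meet weekly with research assistants about matters that include randomization, and weekly with the coaches about participants.
- Under {18b}, group attendance is discussed in weekly team meetings.

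Knowledge of allocation by participant may therefore be spread through the team. An A/B code masks an analyst only if that analyst is kept away from this information.

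**4. How many models are affected?** Secondary questionnaires listed under Secondary outcomes:
- Anxiety and parenting: GAD-7, PSI, PACER, Parenting Scale, PARYC (5)
- Partner relationship: SSEQ, CSI-4 (2)
- Maternal functioning: PROMIS anger, SCS-SF, SISE, PROMIS sleep, DSI-SS, AUDIT, CUDIT-R (7)
- Child: PPSC, ECBQ (2)

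5 + 2 + 7 + 2 = 16. With the PHQ-9, 16 + 1 = 17. Assuming one score per questionnaire and one repeated-measures model per score, this is about 17 models. The ECBQ subset may give more than one score, hence *about*.

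**5. Which analyses could be masked?**
- Can be masked: the primary and secondary mixed models by randomized arm, and moderation by baseline symptom level.
- Cannot be masked: subgroups by telehealth attendance ({20b}), the analysis of those who completed the intervention ({20c}), and anything using app engagement or the weekly surveys. Those data exist only, or mainly, in the BEAM arm and reveal it.

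**The case against.** The strongest reply is that this is an openly disclosed design choice. Section {17a} says plainly who is unblinded and why, and nothing in it is misstated. Much of the main analysis is also fixed: intention to treat, maximum likelihood for missing data, alpha of 0.05. The one model-form decision named, removal of a non-significant quadratic term, is a mechanical rule that gives the same answer with or without arm labels. Masking would need more than a recoded export, because allocation is known within the team. It would also leave the larger problem, an unblinded self-reported PHQ-9, exactly where it is. All of this stands. It limits what masking can achieve, but it supplies no reason for the analyst to see the labels.

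Four stronger readings are tempting, and the documents do not support them.

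- *The article contradicts itself on independence.* Section {31c} says "Data will be analyzed independently and will not be released to any third party", which can look incompatible with analysis by the research team. The sentence goes on to name the funder among those third parties. Read whole, it most naturally means independent of the funder and outsiders, which fits in-house analysis. It could be worded more clearly, no more than that.
- *There are 34 separately settled analyses.* Seventeen outcomes at two change intervals give 17 × 2 = 34 contrasts, but both intervals come from the same repeated-measures model. The count of model decisions is about 17.
- *A key-holder is already in place.* No section says that the randomizing research assistant, or the centre that manages REDCap, keeps the allocation key or is engaged to recode exports. Either might do it, but that has to be arranged.
- *Masking would close off selective subgroups.* The article allows that "Additional subgroup analyses may be explored based on emergent research questions of interest". Such subgroups could still be chosen once the key is released. Prespecification is the remedy for that, and an analysis plan not shown here may provide it.

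**Conclusion.** The point holds as an avoidable risk and an inexpensive improvement. It is not a demonstrated bias or an error of fact. The reason given for unblinded analysts does not support the choice, and the trial already masks its own staff for a less important task.

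The exposure is about 17 primary and secondary outcome models. The size of any resulting bias is unknown and cannot be derived from the documents.

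The conclusion rests on two assumptions. The first is that at least one person able to run the models can be kept from knowing allocation by participant. The second is that someone outside the analysis can hold the key. Neither is stated in the article, and the sponsor should confirm both. If no such analyst exists, that would be a better reason for unblinded analysis than the one now given, and {17a} should state it.

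**What to change.** Amend {17a} to provide that:

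1. A staff member outside the analysis, for example the research assistant who runs the randomization, supplies the outcome file with arm coded A/B and keeps the key.
2. Variables that exist only for BEAM participants (attendance, app use, weekly surveys, app usability) are held in a separate file.
3. The analyst has no access to allocation by ID and stays out of meetings where it is discussed.
4. Cleaning, scoring and the primary and main secondary models are finalised on the masked file, and the code is archived with a date, before the key is released.

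Optionally, {31c} could say that *independently* means independently of the funder.

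**Cost.** One recoded export, a dated code archive and a restriction on one analyst's access and meetings. Whether this needs extra staff time depends on who agrees to hold the key. Attendance, completer and engagement analyses wait until the key is released. Masking may be imperfect if missing data differ clearly between arms. Enrolment, delivery, sample size, alpha and power are untouched, because the change concerns only the analysis stage.
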